## Abstract

**Background:**

Fetal growth restriction (FGR) affects 7–10% of all pregnancies resulting in a higher risk of perinatal morbidity and mortality, long-term disabilities, and cognitive impairment. Due to its multifactorial etiology, changes in maternal lifestyle, including suboptimal maternal diet and stress, have increasingly been associated with its prevalence. We present a protocol for the *Improving Mothers for a better PrenAtal Care Trial Barcelona* (IMPACT BCN), which evaluates two different maternal lifestyle strategies (improved nutrition by promoting Mediterranean diet and stress reduction program based on mindfulness techniques) on perinatal outcomes. The primary objective is to reduce the prevalence of FGR. Secondary aims are to reduce adverse perinatal outcomes and to improve neurodevelopment and cardiovascular profile in children at 2 years of age.

**Methods:**

A randomized parallel, open-blind, single-center trial following a 1:1:1 ratio will select and randomize high-risk singleton pregnancies for FGR (*N*=1218), according to the criteria of the Royal College of Obstetricians and Gynaecologists (19.0–23.6 weeks’ gestation), into three arms: Mediterranean diet, mindfulness-based stress reduction program, and usual care without any intervention. Compliance to the interventions will be randomly tested in 30% of participants with specific biomarkers. Maternal socio-demographic, clinical data, biological samples, and lifestyle questionnaires will be collected at enrollment and at the end of the interventions (34.0–36.6 weeks’ gestation), together with a fetoplacental ultrasound and magnetic resonance. Fetoplacental biological samples and perinatal outcomes will be recorded at delivery. Postnatal follow-up is planned up to 2 years of corrected age including neurodevelopmental tests and cardiovascular assessment. Intention-to-treat and population per-protocol analysis will be performed.

**Discussion:**

This is the first randomized study evaluating the impact of maternal lifestyle interventions during pregnancy on perinatal outcomes. The maternal lifestyle interventions (Mediterranean diet and mindfulness-based stress reduction program) are supported by scientific evidence, and their compliance will be evaluated with several biomarkers.

**Trial registration:**

ClinicalTrials.govNCT03166332. Registered on April 19, 2017

#### Nutrition during pregnancy

The role of maternal and fetal nutrition is well accepted to have a profound impact not only on the early life growth and development, but also on the lifelong health of the individual [15]. Maternal intake of several micronutrients related with fetal growth [16] has been reported to be commonly suboptimal in women from developed countries [17]. In a recent comprehensive metabolomic study [11], we observed alterations in the lipid profiles of FGR fetuses and their mothers. Specifically, mothers of FGR fetuses showed a low concentration of cholesterol and other lipoproteins, which might reflect increased uptake into the placenta and explain the reported increase in circulating triglycerides and cholesterol lipoproteins in growth-restricted fetuses.

Dietary pattern is a key factor in the prevention of several chronic diseases [18]. Concerning pregnancy, rather than individual constituents of food in the form of supplemental intakes of specific micronutrients [19–22], a dietary pattern as a whole may have a great role in achieving optimal maternal nutrition during pregnancy [23]. In this context, the Mediterranean diet (MedDiet), rich in mono- and polyunsaturated fatty acids [24], is an attractive option. Known to reduce the incidence of cardiovascular diseases in adults [18], the MedDiet could as well improve pregnancy outcomes and fetal growth. For instance, in a trial assessing the impact of diet on macrosomia, low adherence to the MedDiet was associated with low birth weight (BW) [25]. In pregnant women from the Generation R study in the Netherlands, both low and medium adherence to the MedDiet was associated with lower BW [10]. In two population-based cohort studies from Spain, higher intakes of fish, legumes, and dairy products were associated with higher infant BW and lower risk of FGR [12]. Similarly, in women from the Danish National Birth Cohort, higher intake of Mediterranean foods reduced the risk for preterm birth [26]. However, all these studies were observational. Therefore, randomized interventional studies powered to test the effect of MedDiet on fetal growth and perinatal outcomes are needed.

#### Stress during pregnancy

The association between maternal stress and FGR has long been described [27]. An over-exposure to stress-induced maternal glucocorticoids has been proposed as a potential mediating mechanism [13, 28]. Evidence in rat models showed that maternal prenatal stress can downregulate the placental enzyme 11β-hydroxysteroid dehydrogenase type 2 (11β-HSD2) [29], essential to oxidize cortisol into cortisone. Recent studies in humans also found direct evidence that maternal prenatal anxiety and depression are associated with a downregulation of the 11β-HSD2 gene expression [30, 31]. Analyses on cord blood samples have revealed higher cortisol and lower adrenocorticotropic hormone levels in cases of FGR [27].

In recent years, accumulating evidence supports the notion that adverse events or external negative stimulus during pregnancy affect maternal psychological well-being and have the potential to alter placental physiology with deleterious consequences in fetal development [14, 32]. In order to reduce stress in pregnancy, a non-pharmacological intervention would be desirable. Mindfulness-Based Stress Reduction (MBSR) is a promising tool for treating anxiety and mood problems in patients with various clinical conditions [33]. There are few published studies on the use of MBRS programs in pregnancy. A recent meta-analysis pooling the results of randomized controlled trials (RCTs) [34] reported a non-significant trend in favor of MBRS interventions to reduce anxiety, depression, and perceived stress. This may be due to a small number of RCTs and participants. The RCTs available were either pilot or feasibility studies, or not adequately powered to demonstrate the effectiveness of a MBSR intervention. A small study suggested that mindfulness-related skills were associated with a reduced chance of delivering a low-BW newborn [35]. Thus, more robust evidence is needed on the impact of MBSR strategies on perinatal outcomes.

#### Justification for the study

Maternal psychological status and dietary pattern are both fundamental for pregnancy well-being and contribute to shape the growth and development of the fetus and future child [36]. The biological plasticity of fetal life renders pregnancy a highly susceptible period for inducing positive effects mediated by lifestyle, particularly in high-risk situations. We hypothesized that lifestyle interventions focusing on improving nutrition and stress well-being could have an impact on improving fetal growth and perinatal outcomes in high-risk pregnancies.

### Objectives {7}

Our main hypothesis is that structured lifestyle interventions to improve nutrition based on MedDiet or to reduce stress with MBSR-based strategies will have an impact in improving fetal growth, perinatal outcomes, and infant development in high-risk pregnancies.

#### Primary objective

The primary objective is to evaluate the impact of the interventions (MedDiet and MBSR) on the rate of FGR at birth.

#### Secondary objectives

The following are the secondary objectives:
(i)To compare the effectiveness of the interventions (MedDiet and MBSR) in terms of reduction of adverse perinatal outcome (APO), defined according to the presence of any of the following perinatal measures: preterm birth, preeclampsia, perinatal mortality, severe FGR, metabolic acidosis, major neonatal morbidity(ii)To evaluate the impact of the interventions (MedDiet and MBSR) on Bayley-III score at 2 years of corrected postnatal age of the infants(iii)To evaluate the impact of the interventions (MedDiet and MBSR) on blood pressure and heart rate at 2 years of corrected postnatal age of the infants

### Trial design {8}

This is a RCT 1:1:1 ratio, parallel, open-blind. The study design adheres to the SPIRIT quality standard criteria for RCT [37].

## Methods: participants, interventions, and outcomes

### Study setting {9}

The study will take place in BCNatal (University Hospitals Clinic and Sant Joan de Déu, University of Barcelona), a large referral center for maternal-fetal and neonatal medicine in Spain, composed of two academic hospitals with more than 7,\000 deliveries/year and extensive experience in perinatal medicine.

### Eligibility criteria {10}

Eligible participants will be pregnant women at high risk to develop FGR during pregnancy according to the criteria of the Royal College of Obstetricians and Gynaecologists (RCOG) (odds ratio (OR) >2) [38].

The inclusion criteria are as follows:
Age ≥18 yearsSpeaking Spanish fluentlyLive singleton non-malformed fetusHigh-risk pregnancy to develop FGR (meeting the criteria of the RCOG)19.0–23.0 weeks of gestation

The exclusion criteria are as follows:
Fetal anomalies including chromosomal abnormalities or structural malformations detected by ultrasound prenatally and congenital infectionsNeonatal abnormalities diagnosed after birthMental retardation or other mental or psychiatric disorders that impose doubts regarding the true patient’s willingness to participate in the studyNo possibility to come to additional visitsIncluded in other RCT studies

### Who will take informed consent? {26a}

Doctors and researcher’s assistants involved in the trial will obtain written informed consent from potential trial participants.

### Additional consent provisions for collection and use of participant data and biological specimens {26b}

An additional written informed consent for biological sample collection will be obtained from the trial participants.

### Interventions

#### Explanation for the choice of comparators {6b}

The interventions are non-pharmacological, based on counseling and behavioral training, and derived from scientific evidence and tested in previous studies [18, 33]: (1) nutrition program based on MedDiet; (2) stress reduction program based on mindfulness techniques, MBSR; and (3) usual care without any intervention.

#### Intervention description {11a}

##### Nutrition program based on MedDiet

The dietary intervention is adapted from the PREDIMED (*Prevención con Dieta Mediterránea)* trial [18]. The main goal of the intervention strategy is to change general dietary patterns rather than focusing on changes in single food or macronutrients. The diet pattern will be adapted to pregnant women in general and will be further adapted after the first individual assessment visit with the dietician, according to the participant’s weight and culture. The intervention will be performed in individual 30-min visits plus a 1-h group session every month. Participants will also be provided with extra-virgin olive oil (2 l every month) and 15 g of walnuts per day (450 g every month) at no cost. Every 2 weeks, the woman will receive a phone call from the dietician in order to reinforce the intervention. Specific materials (recipes, a quantitative 1-week shopping list of food items according to the season of the year, a weekly plan of meals with detailed menus) will be given in each visit and will also be available in the Nutrition section (login with a password given at the moment of randomization) on the trial website (https://fetalmedbarcelona.org/impactbcn/). During each monthly visit, the 17-item dietary screener to assess baseline adherence to the MedDiet will be checked, and a 3-day dietary register will also be evaluated. In addition, blood pressure and weight gained will be measured.

##### Mindfulness-based stress reduction program

The program used for this trial is based on the MBSR program [39], which has been adopted by health institutions and tested in clinical trials [33, 40, 41], but it has been adapted to pregnant women, i.e., with meditations focused on the relationship with the fetus, “being with the baby” informal practice, and prenatal yoga positions. The intervention consists of 8 weekly sessions of 2.5 h plus one-full day session (20–25 people) and daily home practice. There is continuous monitoring/support by dedicated instructors to support practice and provide counseling throughout the 8 weeks and until delivery. Thus, after the program, extra weekly sections with meditations/yoga, sharing moments among women, and pregnancy-related problems will be offered by trained nurses to maintain adherence and practice. During sessions, mindfulness meditation skills are taught to help participants discover relationships between mindful practice and increase the ability to deal more effectively with stress. The sessions include didactic presentations, formal meditation practices, and group discussion. Home practice consists of 45’ of daily formal practice (e.g., sitting and walking meditation, body scan, and yoga stretching) and informal practice (e.g., mindfulness of daily activities and the 3-min breathing space). MP3s/CD of formal meditations adapted to pregnancy are provided for home practice, as well as a book and a notebook with relevant readings and the possibility to register their training. Extra material is also available on the official website of the trial (https://fetalmedbarcelona.org/impactbcn/) in the Mindfulness section (login with a password given at the moment of randomization).

#### Criteria for discontinuing or modifying allocated interventions {11b}

Not applicable due to the nature of the interventions.

#### Strategies to improve adherence to interventions {11c}

##### Participant compliance

Adherence to the nutritional intervention will be assessed by an improvement adherence to the MedDiet, based on an improvement of ≥3 points of their total final score of the 17-item dietary screener compared to their total initial score. The study population will be described according to adherence to the MedDiet, depending on the score: ≥12 high adherence, 6–11 moderate adherence, and <6 low adherence.

Adherence to the MBSR program will be assessed by class attendance and time spent engaged in mindfulness meditation outside of class sessions. The treatment will be considered complete if at least 10 h of meditation is done (both during class and at home), i.e., at least 6 sessions out of 9 are attended.

Biomarkers of compliance will be evaluated in a random sample of 30% of participants among the three arms of interventions, before and after the intervention: biomarkers of compliance with the nutrition program including (i) urinary total polyphenol excretion (adhesion to overall MedDiet pattern), (ii) urinary hydrohytyrosol concentration (compliance of extra-virgin oil), (iii) plasma alpha-linoleic acid concentration (compliance of walnuts), and (iv) biomarkers related to stress (steroid axis) will be evaluated by means of determination of cortisol in maternal 24-h urine [42].

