### Statistical methods

#### Statistical methods for primary and secondary outcomes {20a}

The statistical analysis will follow the general regulatory recommendations given in the ICHE9 Clinical Trials guidelines [53].

The inferential analysis for the main variable (proportion of newborns with a BW below the 10th centile) will be performed by means of OR using a logistic regression model, with a 95% IC. The method of Hochberg will be used for the adjusted *p* values for the comparison of each interventional arm vs. control, i.e., the result *p* values of two comparisons will be ordered descending; the following decisions about the positive results of the study will be considered:
If the highest *p* value will be lowest than the threshold (0.0490), the study is positive for the two interventional arms vs. control.If the highest *p* value will be higher than the threshold (0.0490), the study is not positive for this, and the next variable *p* value should be lowest than the 0.0245 (0.0490/2) to be able to conclude the positive comparison of this interventional arm vs. control.

The specific analysis will be as follows:
Modified intention-to-treat population (mITT), defined as all randomized patients with neonates who did not end with a congenital malformation, diagnosed during pregnancy or in the postnatal period.Population per-protocol (PP), defined as all subjects included in mITT that participated in at least one visit without protocol deviation that might impact the study’s main assessments. The protocol deviation considered in this study is the low compliance with treatments. The next compliance criteria will be a reason for exclusion:
MBSR group: the patient attends less than 6 of 9 sessions (<67%).Nutrition group: the patient has a MedDiet score at final assessment <3 from the initial score.

The patient who withdrew informed consent will be excluded from all populations.

The main study analysis will be performed using the mITT, pre-randomization and baseline analyses, and primary and secondary efficacy analyses. The primary outcome analysis will also be performed using also ITT population as a supportive, PP population to test the robustness of the results.

No inferential analysis will be performed for the baseline comparability.

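### The MedDiet compliance rule counts only a rise of at least 3 points, so women who reach or keep the protocol's own 'high' diet score can be dropped from the per-protocol set

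*Protocol article*

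**What the plan says.** Protocol article, Participant compliance (item 11c): adherence to the nutritional intervention is judged "based on an improvement of ≥3 points of their total final score of the 17-item dietary screener compared to their total initial score". The next sentence gives absolute bands, "≥12 high adherence, 6–11 moderate adherence, and <6 low adherence", for a different purpose: "The study population will be described according to adherence to the MedDiet, depending on the score".

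Statistical methods (item 20a): low compliance is the protocol deviation that removes a woman from the per-protocol population. In the nutrition group the criterion is that "the patient has a MedDiet score at final assessment <3 from the initial score", which I read as a gain of less than 3 points. No exemption for a high starting score is given. The usual care arm has no compliance criterion.

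The same section fixes the role of this population: "The main study analysis will be performed using the mITT". The per-protocol set is used to check the robustness of the primary result.

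Eligibility criteria (item 10) set no upper limit on baseline diet score, so women who already eat well can enrol. Item 18a schedules the MedDiet adherence assessment at enrolment and at the final visit for participants generally, so both scores should exist in every arm.

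**The concern.** A per-protocol analysis is meant to show what happens among women who received the treatment as intended. Here the rule measures how far a woman moved, and the per-protocol definition then treats that as whether she complied. The two differ most for women who start high. They have less room to rise, and regression to the mean works against them, so a woman can follow the diet throughout and still be removed.

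The removal is one-sided. A MedDiet woman who stays at 13 leaves the per-protocol set; a usual care woman who stays at 13 remains. The retained MedDiet women are therefore tilted towards poor starting diets. The protocol's own background section on nutrition cites observational work linking low adherence to the MedDiet with lower birth weight, and the primary outcome is birth weight below the 10th centile. The selection is thus on a factor that the protocol itself ties to the outcome. If the per-protocol and mITT results differ, the difference cannot be put down to the diet having been followed. The MBSR criterion, attendance at 6 of 9 sessions, does not depend on a baseline score in this way.

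**Working it through.** **No stated figure to reproduce.** The protocol gives no score distribution and no expected compliance rate.

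**Step 1: what follows from the cut-offs alone.** Inputs: compliant if final − initial ≥ 3 (items 11c and 20a); 'high' if score ≥ 12 (item 11c). The instrument has 17 items. Its maximum score is not stated; I assume one point per item, range 0–17.

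- Compliance is impossible if initial + 3 > 17, that is, for initial scores of 15, 16 and 17. With a maximum of 16 these become 14–16; with 18, 16–18.
- There are 6 × 6 = 36 pairs with both scores in 12–17. Only six reach a gain of 3: 12→15, 12→16, 12→17, 13→16, 13→17 and 14→17. The other 36 − 6 = 30 are non-compliant.
- Three further pairs enter 'high' from below and are still non-compliant: 10→12, 11→12 and 11→13.

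These are counts of possible score pairs, not of women.

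**Step 2: how many women, under stated assumptions.** Assumed: baseline normal with mean m = 7, 8 or 9 and SD 2.5; final mean m + 3, SD 2.5; baseline–final correlation 0.3 or 0.6; scores rounded and limited to 0–17. I simulated 1,000,000 women per scenario. The share of the arm reclassified by the fix is

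P(final ≥ 12) × P(gain < 3 | final ≥ 12).

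| Baseline mean | Correlation | P(final ≥ 12) | Non-compliant among final ≥ 12 | Product: share of arm reclassified |
|---|---|---|---|---|
| 7 | 0.3 | 27.5% | 14.6% | 4.0% |
| 7 | 0.6 | 27.5% | 19.8% | 5.5% |
| 8 | 0.3 | 42.1% | 20.3% | 8.5% |
| 8 | 0.6 | 42.1% | 24.3% | 10.2% |
| 9 | 0.3 | 58.0% | 26.2% | 15.2% |
| 9 | 0.6 | 57.9% | 29.1% | 16.8% |

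So 15–29% of women finishing at 12 or more are classed non-compliant, and the fix reclassifies 4–17% of the arm. With 406 per arm that is about 0.04 × 406 = 16 to 0.17 × 406 = 69 women, if all have both scores.

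**Step 3: selection on baseline.** In the same scenarios:

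- The chance of being classed compliant is 80–94% with a baseline below 6, and 8–29% with a baseline of 12 or more.
- Compliant women start 1.8–2.4 points lower than non-compliant women.
- Mean baseline in the compliant group lies about 0.8–1.0 points below that of the whole arm. Under the rule 'final ≥ 12 or gain ≥ 3' the shift lies between −0.7 and +0.1, and is smaller in every scenario.

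**The case against.** The best defence is that change is the target. The description of the nutrition programme gives changing overall dietary patterns as its main aim, so a change score is a natural measure of response to counselling. A woman who starts and stays at 13 shows no effect of the programme. This stands as a reason to keep reporting the change. It does not justify excluding her for low compliance, because item 20a uses the score to decide who took the treatment.

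A reader might infer that the two sentences in item 11c contradict each other. They do not: one assesses adherence to the intervention, the other describes the study population's diet. The difficulty is only that the same woman can be 'high' by one and non-compliant by the other.

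A reader might also stress that a woman going from 2 to 5 is adherent while still 'low'. That is possible, but under the assumptions above it concerns about 1% or less of compliant women, and the fix leaves it untouched. Likewise, 24–62% of compliant women would finish below 12, but most of them improved by 3 points into the moderate band. That is not evident misclassification, and I make no claim on it.

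The extreme case is rare too: a start at 15 or more is 0.1–1.4% of women in these scenarios. Women starting at 12–14 can still comply if they gain 3. The weight lies on women who finish 'high' with a smaller gain.

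Finally, diet biomarkers are measured: "Biomarkers of compliance will be evaluated in a random sample of 30% of participants among the three arms of interventions". They give a separate check on the diet received, but they do not enter the per-protocol definition.

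**Conclusion.** The point holds for compliance reporting and for the per-protocol analysis. The rule excludes MedDiet women who reach or keep the protocol's own 'high' score with a gain below 3, and it applies no such filter to usual care. That these women are excluded follows from the text without any assumed distribution. That a start of 15–17 rules out compliance needs the 0–17 scale. The size (15–29% of 'high' finishers, 4–17% of the arm) rests wholly on the assumed means, SD, gain and correlation, and actual scores could fall outside that range.

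One might infer that the trial's primary conclusion is at risk. The documents do not support that: the main analysis is mITT, and this rule enters no primary test, alpha or sample size. Nor can the bias in the per-protocol odds ratio be quantified. Selection towards poor baseline diet would by itself work against MedDiet, but women who respond to counselling may differ in other ways, so the net direction is unknown. This is a correction that should be made, to a supportive analysis.

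**What to change.** In items 11c and 20a, and wherever the SAP repeats the rule, define a MedDiet woman as compliant for the per-protocol set if her final score is at least 12 or it rose by at least 3 points from the initial score. Keep the proportion with a gain of at least 3 as a descriptive measure of response. Report baseline score by compliance status in the MedDiet arm, beside the usual care baseline.

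The cost is one changed sentence in each place; both scores are already collected and the cut-off of 12 is the protocol's own. The downside is that some compliant women will have changed little from baseline. The fix also reduces but does not remove selection after randomisation, so the per-protocol result should still be read with the baseline comparison beside it.
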